**STUDY PROTOCOL**

**SYNOPSIS**

Ty21a - ASC

Cross-reactive immunity elicited by oral and parenteral typhoid vaccines against non-typhoid Salmonellae

| **Version** | **Date** |
| --- | --- |
| Version 2.0 (final) | 15-November-2009 |
|  |  |
|  |  |

Study code

Ty21a - ASC

**Title of the study**Cross-reactive immunity elicited by oral and parenteral typhoid vaccines against non-typhoid Salmonellae

**EudraCT registration**Number: 2009-012949-33

Clinical phase

Phase IV

Indication and rationale

Many Salmonella spp causing gastroenteritis share O antigen serotypes with *Salmonella enteritidis* subsp. *enterica* serovar Typhi (*S.typhi*) and could therefore be in ‚reach‘ of the protective efficacy of the oral live typhoid fever vaccine Vivotif®. Some of these Salmonellae are common causes of diarrhoea in travellers (0-30% of travellers diarrhea depending on the area). In a controlled study in healthy adults the cross-reactivity of the immune response against different Salmonella spp. elicited by Vivotif® shall, therefore, be investigated and compared to the immune response of Typherix®

Study design

Randomized (1:1, Vivotif® vs. Typherix®), controlled, mono-center study

Study objectives

*Primary:*  - Demonstration of cross-reactive antibodies against O9 and/or O12 somatic antigen
 containing Salmonella spp after immunisation with Vivotif (in comparison to
 Typherix®)

*Secondary:*  - To evaluate the homing potentials of circulating vaccine antigen-specific antibody-
 secreting cells towards gut mucosa, systemic immune system and cutaneous sites
 after immunisation with Vivotif® (in comparison to Typherix®)
 - To evaluate the immunogenicity of the typhoid fever vaccine Vivotif® (in comparison
 to Typherix®) in terms of the agglutination antibody response (Widal) and

Salmonella-specific antibody response in serum, saliva and tears (ELISA)

- To analyse the cell-mediated immune response to S.typhi and selected Salmonella

spp (prolifieration assay and IFN-gamma production)

Investigator and study center

[name] MD PhD
Helsinki University Central Hospital, Helsinki, Finland

Study duration planned

Recruitment period: 11 months

First subject first visit: December 2009

Last subject last visit: October 2010

Treatments
The investigational medicinal products (IMP's) are:
Group A - ***Vivotif:* three oral doses administered with an interval of 1 day (Day 0 [Visit 1] and two self-administrations at home on Days 2 and 4). One dose of** Vivotif® (enteric-coated capsule) contains:

- A total of ≥2x109 live *S.typhi* Ty21a bacteria/capsule

Group B - *Typherix***®***:* one intramuscular dose will be administered at Visit 1 (Day 0). One dose (0.5 mL) in a ready-to-use syringe contains:

- 25 mcg of Vi capsular polysaccharide of *S.typhi* Ty2

Number of subjects

50 randomized subjects

**Study Population**

Healthy adults aged ≥18 to ≤65 years (n = 50)

Inclusion criteria

1. Male or female subjects aged ≥18 to ≤65 years
2. General good health as established by medical history and physical examination
3. Written informed consent
4. Females of childbearing potential must agree to use an efficacious hormonal or barrier method of birth control during the study. Abstinence is acceptable.
5. Available for all visits scheduled in this study.

Exclusion criteria

1. Vaccination against typhoid fever within 5 years before dosing.
2. History of clinical typhoid fever, clinical paratyphoid A or B fever.
3. Immunization with any other vaccine (oral or parenteral) within 4 weeks prior to study start or planned vaccination during the study
4. Current intake of antibiotics or end of antibiotic therapy <8 days before first IMP administration
5. Chronic (longer than 14 days) administration of immunosuppressants or other immune-modifying drugs within 6 months before the first dose of IMP; oral corticosteroids in dosages of ≥0.5 mg/kg/d prednisolone or equivalent are excluded; inhaled or topical steroids are allowed
6. Acute or chronic clinically significant gastrointestinal disease
7. Any confirmed or suspected immunosuppressive or immunodeficient condition, including human immunodeficiency virus (HIV) infection
8. Pregnancy or lactation
9. Acute disease at the time of enrollment (defined as the presence of a moderate or severe illness with or without fever (fever is defined as body temperature of ≥38 °C).
10. Alcohol or drug abuse
11. Suspected non-compliance
12. Use of any investigational drug or any investigational vaccine within 30 days preceding the first dose of study vaccine, or planned use during the study period
13. Any clinically significant history of known or suspected anaphylaxis or hypersensitivity reaction based on the judgement of the investigator
14. Employee at the investigational site, relative or spouse of the investigator
15. Any other criteria which, in the investigator’s opinion, would compromise the ability of the subject to participate in the study, the subject’s well-being, or the outcome of the study

Criteria for evaluation

*Primary endpoint:*

- Measurement of specific IgA -, IgG- and IgM-secreting antibody cells specific to / cross-reactive with the different Salmonella serovars in peripheral blood using ELISPOT

*Secondary endpoints:*

- To evaluate the expression of various homing receptors (intestinal, systemic, cutaneous) on antigen-specific antibody-secreting cells by separation the PBMCs with immunomagnetic cell sorting according to their HR expressions and by investigating specific ASC in the resulting subpopulations
- Anti-Salmonella spp. agglutination antibody response in serum (Widal test)
- Anti-Salmonella antibodies in serum, saliva or tears (ELISA)

Procedures

- Screening for eligibility (inclusion/exclusion criteria)
- Gender stratification
- Randomization 1:1 to receive Vivotif**®** (Group A) or Typherix**®** (Group B)
- 1st Blood sampling prior to 1st administration of IMP on Day 0 (Visit 1)
- Immunization on Days 0, 2 and 4 with Vivotif**®** and on Day 0 with Typherix**®**, respectively
- Recording of unsolicited AEs and of SAE's throughout the whole study
- 2nd Blood sampling 7 days after administration of 1st dose of Vivotif**®** and of the single dose of Typherix**®** ,i.e. on Day 7 for group A and group B, respectively
- Telefone contact on Day 26±1 to enquire on any intercurrent AE and remind the subject re Visit 3 (Day 28±3)
- 3rd Blood sampling 4 weeks (Day 28±3) after study start

AEs and SAEs will be reviewed, documented and reported up to Visit 3 (Day 28 ± 3). Subjects will be instructed to report any SAEs perceived during 6 months after the last test IMP administration.

Contraindications will be checked for every subject before vaccination. Females of childbearing potential must make an oral statement confirming that they are not pregnant and they will be instructed to report a pregnancy occurring/becoming known during the study period (these will have to be followed-up until birth and the outcome reported to Berna Biotech-Crucell)

**Statistical methods***Sample size*

No sample size calculation has been performed. The group size is considered to be sufficient to detect and document the difference in cross-reactivity of the immune response between Vivotif**®** and Typherix**®**.

A total of 50 subjects will be randomized in a 1:1 ratio to Vivotif**®** or Typherix**®**.

Categorical data will be presented in contingency tables along with frequencies and percentages. Continuous data will be summarized using at least the frequency (n), mean, standard deviation, median and the range. Descriptive analyses for demographic baseline characteristics will be presented for all subjects and by treatment group for the total population and the subsets.

Adverse events (AEs will be presented using descriptive statistics (incidence rates). Any serious adverse events (SAEs) and discontinuations due to adverse events will be described in detail. In addition, all data will be reported in subject listings.

The results of antibody secreting cells (ASCs) will be given as ASC / 106 PBMC. These data are used to calculate geometric means ± SEM; the two groups will be compared with each other with Student’s t-test.

The expression of homing receptors on ASC will be documented as percentages of ASC expressing the given marker. These data are used to calculate arithmetic means ± SD; the two groups will be compared with each other with Student’s t-test.

The geometric mean titers (GMTs) and corresponding 95% CIs of the Widal agglutination antibodies will be presented together with a descriptive summary (mean, standard deviation [s.d.]) of the original antibody values by study group and visit.

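### The protocol fixes no single primary variable: isotype, serovar set and sampling day are all left open, so the comparison that counts as demonstration can be picked after the data are seen

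*Protocol*

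**What the plan says.** **Objective.** Under Study objectives, the primary aim is "Demonstration of cross-reactive antibodies against O9 and/or O12 somatic antigen" containing Salmonella spp after Vivotif, in comparison to Typherix. No strains are listed, and nothing says what result would amount to demonstration.

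**Endpoint.** Under Criteria for evaluation, the primary endpoint is "Measurement of specific IgA -, IgG- and IgM-secreting antibody cells specific to / cross-reactive with the different Salmonella serovars", measured in peripheral blood by ELISPOT. That gives three isotypes and an uncounted set of serovars, with no visit.

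**Sampling.** Under Procedures, blood is taken before the first dose on Day 0, then "2nd Blood sampling 7 days after administration of 1st dose of" Vivotif (the same day in the Typherix group), and finally "3rd Blood sampling 4 weeks (Day 28±3) after study start". Figure 1 repeats these three draws. Neither place ties a draw to the primary endpoint.

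**Analysis.** Under Statistical methods, ASC results are expressed per million PBMC: "These data are used to calculate geometric means ± SEM; the two groups will be compared with each other with" Student's t-test. The sentence covers all ASC results alike.

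**Sample size.** The protocol says openly that no calculation was done, then adds: "The group size is considered to be sufficient to detect and document the difference in cross-reactivity". Fifty subjects are randomised 1:1, so 25 per arm. No significance level, sidedness, effect size or standard deviation is given.

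**The concern.** A randomised comparison that sets out to demonstrate something has to say in advance which result would demonstrate it. Here three choices are open at once: which isotype (or the total), which serovar or set of serovars, and which visit. Each combination yields its own two-group comparison, and the protocol treats all of them as primary.

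Objective and endpoint also do not cover the same ground. The objective is limited to strains carrying O9 and/or O12. The endpoint's phrase "cross-reactive with the different Salmonella serovars" has no such limit, and because the endpoint counts cells specific to as well as cross-reactive with the serovars, it can take in the vaccine serovar itself, which is not a question of cross-reactivity.

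Two things are at stake. If one favourable comparison is reported as the primary result, its nominal error rate is not the real one. And whether 25 per arm is enough cannot be judged until it is known which comparison, or how many, must carry the claim.

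**Working it through.** The protocol gives no figure to reproduce: 50 is stated without a calculation. What follows sizes the consequence of leaving the primary variable open.

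**Inputs from the protocol**
- Isotypes: 3 (primary endpoint).
- Post-dose draws: 2, Day 7 and Day 28 ± 3 (Procedures).
- Subjects: 50, allocated 1:1, so 25 per arm (Sample size).

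**Assumptions, not in the protocol**
- Two-sided 0.05 per test, no adjustment.
- Number of serovars: taken as 1, 3 or 4 to give a range.
- Correlation between comparisons: from 0 to 0.9, equal for all pairs.
- All 25 per arm evaluable.

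**Number of comparisons (isotypes × serovars × visits)**
- 3 × 1 × 1 = 3
- 3 × 4 × 1 = 12
- 3 × 3 × 2 = 18

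**Chance of at least one false positive.** For independent tests it is 1 − 0.95^m:
- m = 3: 1 − 0.857 = 14.3%
- m = 12: 1 − 0.540 = 46.0%
- m = 18: 1 − 0.397 = 60.3%

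The comparisons share the same subjects' blood, so independence is an upper bound. For correlated tests, two-sided t-tests with 25 per arm were simulated with no true difference:

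| Tests | Independent | Corr. 0.5 | Corr. 0.7 | Corr. 0.9 |
| --- | --- | --- | --- | --- |
| 3 | 14% | 13% | 11% | 8% |
| 12 | 46% | 32% | 24% | 14% |
| 18 | 60% | 40% | 28% | 15% |

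The simulated cells come from 100,000 runs; shorter runs move them by up to about one percentage point. Every cell is above 5%.

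Counting only false results that favour Vivotif gives about half of the correlated figures: at correlations 0.5 and 0.9 respectively, 6% and 4% for 3 tests, 16% and 7% for 12, and 20% and 8% for 18. The matching reference for a single two-sided 5% test is 0.05 / 2 = 2.5%.

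**Detectable difference at 80% power, 25 per arm.** The two-sample t-test has 50 − 2 = 48 degrees of freedom and noncentrality d × √(25/2) = 3.54 d, where d is the difference in SD units. Solving for 80% power:
- one comparison, level 0.05: d = 0.81
- Bonferroni over 3, level 0.05 / 3 = 0.0167: d = 0.94
- Bonferroni over 12, level 0.05 / 12 = 0.0042: d = 1.10
- Bonferroni over 18, level 0.05 / 18 = 0.0028: d = 1.14

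At a true difference of 0.8 SD, power is 79% for one named comparison and 44% for each of 12 under Bonferroni. The adequacy of the group size therefore depends on the choice that the protocol leaves open.

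**The case against.** The strongest reply is that the protocol states no rule that could be called wrong. Three stronger readings are tempting, and the text does not support them.

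- **That any single p below 0.05 will be declared success.** The protocol gives no level, no sidedness and no success criterion. The wording leaves this possible; it does not say it.
- **That the comparisons are tested without adjustment.** The t-test sentence neither applies nor excludes adjustment. Multiplicity handling is commonly left to the SAP, which is not at hand, so silence on it is not the defect.
- **That the objective's and/or makes success a union of tests.** Read in full, the phrase says which somatic antigens the strains contain: O9, O12 or both. It describes a class of strains, not a decision rule.

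It is also fair to say that the larger percentages need independence, which is implausible for isotypes and related serovars measured in the same blood, and that the serovar counts are assumed. The study is small, single-centre and makes no formal power claim. The comparison also has an expected direction, which roughly halves the correlated error rates.

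All of that stands, and it narrows the point. It does not remove it. Naming the isotype or composite, the serovars and the visit of a primary endpoint is the protocol's task. This protocol does state a primary endpoint and a test for it, and leaves all three open. The admission that no sample size was calculated is candid, but the sentence after it still asserts that a difference can be detected, for a comparison that has not been defined.

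**Conclusion.** The point holds in this form: the protocol fixes no single primary variable and no criterion for demonstration, and its endpoint is wider than its objective. The result reported as primary can be selected after the data are seen.

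The size can only be given as a range. If such a selection were made at an assumed two-sided 0.05 per test without adjustment, the false-positive chance would be about 8–14% over three isotypes alone, 14–46% over 12 comparisons and 15–60% over 18. The lower ends assume correlation 0.9 and the upper ends independence. The lower ends are the modest case, and even there the two-sided rate exceeds 5%. These figures show what the open definition permits, not what the sponsor intends to do. The defect in the definition does not depend on them.

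**What to change.** In the protocol, name one primary variable by fixing three things: one isotype or the total; one named non-typhoid serovar, or a defined set, within the O9 and/or O12 class; and one visit. Total specific ASC at Day 7, compared on the log scale, would be one workable example. The choice is the sponsor's; the essential step is to make it before the data are seen.

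Then test the other O9/O12 comparisons in a stated fixed sequence or by Holm, and make the remaining isotypes, visits and serovars supportive. Align the endpoint's wording with the strain class of the objective.

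Replace the assertion that the group size suffices with the detectable difference for the named comparison: about 0.81 SD on the analysis scale, with 25 evaluable per arm, 80% power and two-sided 5%. State that level in the protocol.

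The change is to wording only; no sample, visit or assay is added. The small cost is that fewer comparisons can carry a confirmatory claim.

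### The primary ASC analysis attaches an additive SEM to a geometric mean, names no scale for Student's t-test, and uses a summary that fails on a zero count

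*Protocol*

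**What the plan says.** The primary endpoint (Protocol, Criteria for evaluation) is "Measurement of specific IgA -, IgG- and IgM-secreting antibody cells specific to / cross-reactive with the different Salmonella serovars in peripheral blood using ELISPOT". Under Statistical methods, "The results of antibody secreting cells (ASCs) will be given as ASC / 106 PBMC" (the 106 is 10 to the power 6, with the exponent lost in text extraction). The next sentence gives the whole analysis: "These data are used to calculate geometric means ± SEM; the two groups will be compared with each other with Student’s t-test".

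Two neighbouring paragraphs help in reading it. For the homing-receptor percentages the plan says "These data are used to calculate arithmetic means ± SD; the two groups will be compared with each other with Student’s t-test", so the t-test clause is the same but the summary is arithmetic. For the Widal titres it says "The geometric mean titers (GMTs) and corresponding 95% CIs of the Widal agglutination antibodies will be presented", so that geometric mean gets a confidence interval.

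No log transformation is mentioned anywhere, and there is no rule for zero counts. On size: "A total of 50 subjects will be randomized in a 1:1 ratio to Vivotif" or Typherix, with an express statement that no sample size calculation was done.

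**The concern.** Choosing a geometric mean treats the ASC counts as data whose natural scale is logarithmic. The rest of the sentence does not follow through, in three ways.

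- **Error bar.** Uncertainty around a geometric mean is multiplicative. Geometric mean plus or minus an SEM mixes two scales if the SEM comes from the raw counts. If it comes from the logs, it cannot be added to or subtracted from a back-transformed mean.
- **Test.** Student's t-test compares arithmetic means on whatever scale the values are entered. The identical clause for the homing-receptor percentages appears to mean untransformed values. Read the same way here, the p-value would concern a different quantity from the one in the table.
- **Zeros.** A single zero makes the plain geometric mean 0 and the log undefined. The Protocol gives reason to expect some: Group B's dose is listed as "25 mcg of Vi capsular polysaccharide of" *S. typhi* Ty2, the primary objective concerns O9 and O12 somatic antigens, and one blood sample is taken before dosing.

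At stake are the displayed precision, whether the comparator group's summary can be computed, and possibly power. Scale and zero handling could also be chosen after the data are seen.

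**Working it through.** The Protocol states no power, alpha, SD, effect size or zero rate, so there is no figure to reproduce.

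**Inputs.** From the Protocol: 50 subjects, 1:1, so n = 25 per group. Assumed: two-sided alpha 0.05; log-normal ASC with ln-SD s of 0.5, 1.0, 1.5 or 2.0, equal in both groups; a three-fold difference in geometric means; a geometric mean of 30 per million PBMC where a level is needed.

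**1. Error bar, if the SEM is taken from raw counts.** SEM = SD/√25 = SD/5. In simulated samples of 25 the median ratio of SEM to geometric mean is 0.11, 0.32, 0.83 and 2.08 at s = 0.5, 1.0, 1.5 and 2.0. With a geometric mean of 30, a typical display at the last three values is about 30 ± 10, 30 ± 25 and 30 ± 63. The lower bar is negative in about 0%, 1%, 38% and 85% of samples. The coherent one-SE form is a factor exp(s/5): 1.11, 1.22, 1.35 and 1.49, multiplied and divided.

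**2. Zeros.** P(at least one zero among 25) = 1 − (1 − p)^25 for a per-subject zero rate p:

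| p (assumed) | P(at least one zero) |
|---|---|
| 2% | 40% |
| 5% | 72% |
| 10% | 93% |
| 30% | >99.9% |

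**3. Which quantity is tested.** Under log-normality, arithmetic mean = geometric mean × exp(s²/2). With equal s the two ratios agree. With unequal s they do not: equal geometric means with s = 1.5 and s = 1.0 give an arithmetic ratio of exp((2.25 − 1.00)/2) = exp(0.625) = 1.87.

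**4. Power for a three-fold difference.** On logs the standardised difference is ln 3/(s√(2/25)) = 1.0986/(0.2828 s) = 3.88/s. The normal approximation Φ(3.88/s − 1.96) gives 97%, 74% and 49% at s = 1.0, 1.5 and 2.0. Simulation with the t-test gives:

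| s | Raw-scale t | Log-scale t | Loss (points) |
|---|---|---|---|
| 0.5 | 100% | 100% | 0 |
| 1.0 | 85% | 97% | 12 |
| 1.5 | 37% | 72% | 35 |
| 2.0 | 13% | 48% | 35 |

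The raw figures move by a point or two between simulation runs. At s = 0.5 both tests are at their ceiling. For a smaller difference of 0.8 SD on the log scale, power at s = 0.5 is 74% raw against 79% on logs.

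**5. Type I error of the raw-scale test.** It falls from 4.6% at s = 0.5 to 2.1% at s = 2.0, so it is conservative and not inflated.

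**6. Effect of the value put in for zeros.** Suppose responders have a geometric mean of 30 in both groups, with 45% zeros in Group B and none in Group A. Replacing each zero by v gives a geometric mean ratio of (30/v)^0.45: 13.0 for v = 0.1, 4.6 for v = 1 and 1.6 for v = 10.

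**The case against.** The strongest reply is that the sentence is incomplete, not wrong. It does not say that the SEM is arithmetic or that the t-test uses raw values. A log-scale SEM and a t-test on logs are the usual companions of a geometric mean; if those are meant, the test fits the summary and no power is lost. The document is headed a synopsis, and a SAP that is not shown may fix the transformation and the zero rule. The general paragraph also promises mean, SD, median and range for continuous data, plus subject listings, so skew and zeros would be visible and Group B would not lack every summary. Giving Widal a CI and ASC an SEM is a difference in display, not a contradiction.

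Most of this stands, and it limits the point. A reader might infer that the plan prescribes an arithmetic SEM and raw-scale testing, that the data are zero-heavy, and that a large loss of power follows. The Protocol supports none of these as fact. The first is a natural reading of the wording, but not its content. The second has no figure behind it: the vaccine content makes zeros plausible at an unknown rate. The third needs both raw-scale testing and strong skew. With 30% against 10% zeros, a two-fold ratio and ln-SD 0.5, the raw test had more power than a t-test on log(x+1) (99.6% against 91%). No planned power is lost either, as none was stated. Day 0 zeros affect only the summary, because no Day 0 group test is announced.

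The reply does not rescue the sentence as written. The additive SEM is wrong for a geometric mean on either reading, and on the log reading a single zero stops both the summary and the test.

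**Conclusion.** The point holds in limited form and is a should-fix. The one stated group comparison for the primary endpoint pairs a geometric mean with an unsuitable error bar, leaves the scale of the test open, and rests on a summary that fails at the first zero. These follow from the wording and need no distributional assumption.

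The cost in power is conditional. With log-normal data, equal spread, 25 per group, two-sided 0.05 and a three-fold difference, raw-scale testing costs about 12 points at ln-SD 1.0 and about 35 at ln-SD 1.5 and 2.0. It costs nothing at ln-SD 0.5, or at any spread if the test is on logs. False-positive risk is not raised. The zero rates are assumptions, and the Protocol gives no value for spread or effect.

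**What to change.** Replace the ASC sentence, before any analysis, with text to this effect:

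*ASC per million PBMC will be analysed after log10 transformation. Zero counts will be set to a value fixed in advance from the assay's detection limit. Geometric means will be shown with back-transformed 95% CIs. Groups will be compared by a t-test on the log values, reporting the geometric mean ratio with its 95% CI. A Wilcoxon rank-sum test and the proportion of responders in each group, with the responder definition fixed in advance, will be reported alongside in every case.*

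The last sentence matters: the rank test and responder proportion should be planned outright, not brought in according to the share of zeros observed, since that would let the data select the test.

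The change costs a paragraph of text and no new data or visits. Its downside is that, with many zeros, the geometric mean ratio depends materially on the substituted value, as step 6 of the working shows. The ratio should therefore be reported with a sensitivity analysis over that value. The rank test supports the p-value in that situation, but it does not stabilise the ratio.

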**Figure 1: Schedule of assessments**

|  | **Visit 1** Baseline |  |  | **Visit 2** | **Visit 3** |
| --- | --- | --- | --- | --- | --- |
| Timing | Day 0 | Day 2 | Day 4 | Day 7 | Day 28 ± 3  *(Days 25 to 31)* |
| Informed consent | X |  |  |  |  |
| Inclusion/exclusion criteria | X |  |  |  |  |
| Demography and medical history | X |  |  |  |  |
| Physical examination | X |  |  |  |  |
| Contraindications a | X |  |  |  |  |
| Gender stratification / Randomization | X |  |  |  |  |
| Blood sampling | X |  |  | X | X |
| Vivotif**®** /Typherix**®** administration | Xb | Xc | Xc |  |  |
| Adverse events d | X |  |  | X |  |
| Concomitant medication | X |  |  | X |  |

a To be performed pre-dose.
b Subjects will be closely observed for 20 min after the 1st IMP administration.

c Subjects in the Vivotif**®** group will self-administer the vaccine at home.

d Subjects are instructed to report any SAEs perceived during 6 months after last IMP administration.

**References**- Kantele A et al. Specific immunoglobulin-secreting human blood cells after peroral vaccination
 against Salmonella typhi. J Infect Dis 1986; 153: 1126-31

- Kantele A: Antibody secreting cells in the evaluation of the immunogenicity of an oral vaccine,
 Vaccine 1990;8:321-6

- Kantele A, Arvilommi H, Kantele JM, Rintala L, Mäkelä PH: Comparison of the human immune
 response to live oral, killed oral or killed parenteral *Salmonella typhi* Ty21a vaccines, Microbial
 Pathogenesis 1991;10:117-26

- Kantele A, Kantele JM, Savilahti E, Westerholm M, Arvilommi H, Lazarovits A, Butcher EC, Mäkelä
 PH: Homing potentials of circulating lymphocytes in humans depend on the site of activation: oral,
 but not parenteral, typhoid vaccination induces circulating antibody-secreting cells that all bear
 homing receptors directing them to the gut, J Immunol 1997;158:574-9

- Kantele A et al. Unique characteristics of intestinal immune system as inductive site after antigen
 re-encounter. J Infect Dis 2005; 191: 312-317

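### Randomisation is stratified by gender, but the two named between-group tests have no gender term and are conservative if gender predicts the response

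*Protocol*

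**What the plan says.** Gender is the only stratification factor named. The Procedures list has "Gender stratification" directly before the 1:1 randomisation step, and Figure 1 (Schedule of assessments) joins the two in one row, "Gender stratification / Randomization". On size, the protocol states: "A total of 50 subjects will be randomized in a 1:1 ratio to Vivotif", which gives 25 per arm.

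The Statistical methods section names a between-group test for two outcomes:

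- ASC, the primary endpoint: "These data are used to calculate geometric means ± SEM; the two groups will be compared with each other with Student’s t-test".
- Homing receptors, a secondary endpoint: "These data are used to calculate arithmetic means ± SD; the two groups will be compared with each other with Student’s t-test".

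Both sentences end on the same clause, "the two groups will be compared with each other with Student’s t-test", and neither mentions gender. For the Widal titres the plan is descriptive: "The geometric mean titers (GMTs) and corresponding 95% CIs of the Widal agglutination antibodies will be presented together with a descriptive summary", by group and visit, with no test between groups. No comparison is stated for the ELISA or cell-mediated outcomes. On power, the protocol says: "No sample size calculation has been performed".

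**The concern.** The design conditions on gender and the named analysis does not. When gender is balanced between arms, differences between men and women cannot contribute to the treatment difference, so the true sampling variance of that difference falls. The pooled SD in Student's t-test still contains those differences. If they are real, the standard error and p-value describe a less precise trial than the one that was run.

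What is at stake is some power. With 50 subjects and no sample size calculation, the protocol shows no known margin to absorb a conservative test.

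**Working it through.** The protocol gives no power, effect size, SD or significance level, so there is no figure of its own to reproduce.

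**Inputs from the protocol.** 50 subjects at 1:1, so 25 per arm; stratification by gender; Student's t-test, with 25 + 25 − 2 = 48 degrees of freedom.

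**Assumptions.** Two-sided alpha of 5%; gender exactly balanced between arms; a gender effect that is additive and equal in both arms; R², the share of within-arm outcome variance explained by gender, varied from 0 to 0.30.

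**Formula.** Set the total within-arm variance to 1.

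- The t-test takes the standard error of the difference to be about √(2/25) = 0.283.
- With gender balanced, the true standard error is √((1 − R²) × 2/25).
- The ratio of the two is 1/√(1 − R²).

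This gives 1/√0.95 = 1.026, 1/√0.90 = 1.054, 1/√0.80 = 1.118 and 1/√0.70 = 1.195.

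**Scale of R².** With a near-even gender split, a gender difference of d within-gender SDs gives R² = 0.25d²/(1 + 0.25d²). So d = 0.5 gives 0.0625/1.0625 = 6%, d = 0.8 gives 0.16/1.16 = 14%, and d = 1.0 gives 0.25/1.25 = 20%.

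**Reference effect.** With 25 per arm, the t-test has 80% power at a standardised difference of about 0.81 (noncentral t).

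**Simulation.** 40,000 trials per setting, 25 per arm, 24 of one sex and 26 of the other, comparing the t-test (48 df) with a linear model on arm and gender (47 df). Power is at a difference of 0.81 total SD.

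| R² (assumed) | Reported SE, t-test ÷ adjusted | Type I error, t-test | Type I error, adjusted | Power, t-test | Power, adjusted |
|---|---|---|---|---|---|
| 0 | 1.00 | 5.0% | 5.0% | 80% | 80% |
| 0.02 | 1.01 | 4.8% | 5.0% | 80.1% | 80.6% |
| 0.05 | 1.03 | 4.5% | 5.0% | 80.4% | 81.8% |
| 0.10 | 1.06 | 3.8% | 4.8% | 81% | 84% |
| 0.20 | 1.12 | 2.9% | 5.0% | 82% | 88% |
| 0.30 | 1.20 | 2.0% | 4.9% | 84% | 92% |

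The simulation error of a 5% rate is √(0.05 × 0.95/40,000) = 0.1 percentage point. A 72/28 gender split gives nearly the same results.

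If the treatment effect is instead fixed at 0.8 *within-gender* SD, adjusted power stays at 79%. The t-test has 77%, 75% and 72% for gender differences of 0.5, 0.8 and 1.0 SD. The comparison of the two analyses leads to the same conclusion on either scale.

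**Direction.** With gender balanced, the estimated difference is the same with or without the gender term. Only the standard error and what follows from it change, and the t-test errs on the cautious side.

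**The case against.** The strongest objection is that the loss may be nil. The protocol gives no reason for stratifying by gender and no evidence that gender affects ASC or homing. At R² of 0.05 or less, the standard error is at most about 3% too large and power differs by about 1.5 points. This stands, and it is why the point must be conditional.

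The balance assumption is also open, because the randomisation mechanism is not described. If assignment were unrestricted within each gender, balance would not be assured and the t-test would be closer to its nominal level. The treatment contrast may also be large: the comparator contains Vi polysaccharide, while the primary objective concerns the O9 and O12 antigens. A slightly conservative test would then matter little, and an equal gender shift in both arms would be doubtful. That is an inference, not a figure in the document, but it is a fair one.

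It can also be said that covariates belong in an analysis plan, which is not shown and may add gender. This carries less weight, because the protocol does not leave the choice open: it names the test.

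A reader might infer more than the text supports:

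- *That every group comparison ignores the stratum.* Only two tests are named; no between-group test is stated for the Widal titres.
- *That the precision gained by stratifying is lost.* Balance still reduces the true variance of the difference. What is missing is credit for it in the reported standard error and p-value.
- *That confidence intervals will be too wide.* No interval for a treatment difference is planned. The only ones are for Widal titres within each group, to which this argument does not apply.
- *That the results would be invalid.* There is no bias and no inflation of type I error.

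**Conclusion.** The mismatch between design and analysis is in the text and concerns the two named tests, for ASC and homing receptors. Its effect depends on two things the protocol does not show: that gender predicts the response, and that stratification achieves balance. If both hold, the reported standard error is too large, from about 3% at R² = 0.05 to 12% at R² = 0.20, and the test is conservative by the amounts tabulated. If gender has no effect, nothing is lost. The severity is minor: the case for change rests on the correction being almost free, not on any threat to a positive finding.

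**What to change.** In the Statistical methods section:

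- **ASC:** replace the t-test by a linear model on log ASC with treatment and gender as factors. Report the gender-adjusted ratio of geometric means with its 95% CI. Zero counts need a stated rule, but the planned geometric means already need one.
- **Homing receptors:** use a linear model on the percentage scale with treatment and gender, or a gender-stratified rank test (van Elteren). Do not take logs: the protocol summarises these data as arithmetic means, and a percentage can be zero.
- **Serology:** add the gender term only if a between-group comparison is made.

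The cost is a short text change and one degree of freedom (47 instead of 48), with no visible loss of power when gender has no effect. Gender is already recorded for randomisation, so no further data are needed.
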